**8. Discontinuation criteria**

1.Serious adverse events occurred during the trail, such as severe cardiovascular and cerebrovascular emergencies, seizures with cardiac arrest, status epilepticus, or other symptoms of serious mental illness.

2.Adverse events occurred during the trail, including allergy to antiplatelet drugs or intolerable side effects, etc.

3.Participants with incomplete data or serious violation of the protocol.

For subjects who are lost to follow-up, attempts to contact the subject will be documented on a Discontinuation CRF. If the subject fails to comply with at least one follow-up visit, the study center must make attempts to contact the subject. There must be at least three attempts to contact the subject, which includes one attempt via registered mail. Details of the attempts must be documented in the subject’s chart.

**9. Adverse Events**

Adverse events are defined as an undesirable health occurrence or untoward deviation in health away from baseline, whether or not device or procedure related.

All adverse events occurring after enrollment (enrollment is defined as point of randomization) for either study group will be collected on the adverse event form and analyzed according to the statistical plan. All adverse events will be continued to be followed until resolution or no resolution is expected.

An independent Data Safety Monitoring Board (DSMB) has been formed to regularly review study progress with regard to safety. Members of the DSMB have no affiliation with the PFO Occluder clinical study. This committee is composed of three clinicians (one Adult Cardiologist, one Neurologist and one Interventional Neuro-radiologist) and a Biostatistician.

The primary responsibilities of the DSMB are to:

1.Establish adverse event definitions (and refine definitions as necessary during the

conduct of the study).

2.Review and adjudicate adverse events as they occur over the course of the study.

3.Review of all failure criteria.

4.Review and validate the patient sample (i.e., inclusion/exclusion deviation and other protocol deviations).

5.Provide oversight for issues affecting general patient welfare.

At any time during the course of the study, the DSMB may offer opinions or make formal recommendations concerning aspects of the study impacting patient safety (e.g., safety related protocol changes or input regarding adverse event rates associated with the Investigational study). Additionally, the DSMB may act as an advisory panel for questions regarding Informed Consent, patient entry, protocol implementation, study endpoints, core lab, Investigator discrepancies, and other issues that may present during the course of the study.

1. Unanticipated Adverse Events: shall be reported by the Investigator to the reviewing IRB as soon as possible, but in no event later than 10 working days after the Investigator first learns of the event.

The Sponsor shall report to all reviewing Institutional Review Boards and participating Investigators, any unanticipated adverse events within 10 working days after the Sponsor first receives notice of the event.

2. Anticipated Adverse Events: adverse events will be classified as either serious adverse events, adverse events or other events and will be identified as either device related, procedure related or “other” (such as pre-existing conditions).

Device failures would include but are not limited to: device removal (due to embolization or misplacement), thrombus formation on the device surface with the risk of subsequent embolization, infectious endocarditis, device collapse due to structural failure, and cardiac perforation due to the presence of the device.

The DSMB met to develop the adverse event definitions. All reported adverse events will be evaluated and categorized as either Serious Adverse Event, Adverse Event, or Other Event based on the following definitions. The DSMB will have the final rule on all adverse events categorizations.

a. Serious Adverse Events

Death, life threatening adverse event, inpatient hospitalization or prolongation of existing hospital stay, persistent or significant disability/incapacity, congenital anomaly/birth defect, and medically significant event, including laboratory abnormalities.

b. Adverse Events

Any reported adverse event not categorized as serious adverse events or other events. Adverse events are defined as an undesirable health occurrence or untoward deviation in health away from baseline, whether or not device or procedure related.

c. Other events

Reported events deemed not to be adverse events by the DSMB. These events may be changes from baseline but not untoward medical occurrences.

The DSMB further defined the following Anticipated Adverse Events. The above mentioned definitions will be applied to the following events to categorize severity. Strong consideration will be given in the determination of procedure or device related for events occurring within 30 days of the procedure. These potential events include, but are not limited to:

Anticipated Adverse Events

Air embolus – symptomatic event resulting from introduction of air into circulatory system

Allergic dye reaction – idiosyncratic reaction to dye used in imaging

Allergic drug reaction – idiosyncratic reaction to drugs used

Anesthesia reactions – idiosyncratic reaction to anesthetic agent used

Apnea – cessation of breathing

Arrhythmia – cardiac rhythm disturbance

Bacterial endocarditis – documented infection of vascular structures including cardiac and related blood vessels

Bleeding – loss of blood from vascular system requiring 1 unit of blood or >5g/dl drop in Hb.

Brachial plexus injury – neurological symptom resulting from damage to brachial

plexus

Cardiac perforation – physical penetration of cardiac structures

Cardiac Tamponade

Chest pain

Device embolization – detachment of a device or its part from intended location

Device erosion

Death

Fever – ≥ 101.5F

Headache/migraine – neurological symptoms attributable to migraine

Hypertension – sustained BP > 140/90mmHg

Hypotension – sustained BP < 90/60mmHg

Myocardial infarction – 2 of the 3 (increased troponin, EKG change, typical chest

pain symptom)

Pacemaker placement secondary to PFO device closure

Palpitations – mild, unsustained

Pericardial effusion – fluid collection around heart documented on 2D-echo

Peripheral embolism – symptom consistent with arterial embolism

Pericarditis – A disorder caused by inflammation of the pericardium, which is the

sac-like covering around the heart

Pleural effusion – excessive fluid in the pleural cavity

Pulmonary embolism – A blockage of an artery in the lungs by fat, air, clumped

tumor cells or a blood clot

Reintervention for device removal

TIA: Acute focal neurological deficit (defined as focal motor deficit, aphasia, difficulty walking, hemisensory deficit, amaurosis fugax, blindness, or focal visual

deficit) presumed due to focal ischemia; symptoms persisting greater than or equal to 5 minutes and less than 24 hours, that is not associated with MR or CT findings of a new, neuroanatomically relevant cerebral infarct.

Thrombus – mass detected on device consistent with thrombus

Valvular regurgitation – Regurgitation of blood from any of the 4 cardiac valves, of more than “mild” severity defined by transthoracic color-flow echo.

Vascular access site injury – damage at vascular access site (i.e. AV fistula, aneurysm)

3. Event Board

A separate Event Board consisting of an Adult Cardiologist, a Neurologist and a Neuroradiologist. The responsibility of the Event Board is to adjudicate events related to primary and secondary neurological endpoint criteria. The Event board will be blinded to the subject’s treatment. The Event Board Committee will have final adjudication responsibilities for subject outcomes related to primary and secondary neurological endpoint criteria.

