**6. Interventions**

**6.1 Intervention grouping**

Participants in the PFOC-RE trial will be randomly assigned to either the surgical intervention group or the control group. The surgical intervention group will undergo PFO closure surgery and receive antiplatelet therapy for six months. This therapy will include 75mg of clopidogrel and 100mg of aspirin daily for the first three months. From the fourth to the sixth month, the participants will switch to taking 100mg of aspirin daily. Meanwhile, the control group will not receive PFO closure surgery but will still need to undergo antiplatelet therapy for six months with the same medication regimen as the surgical intervention group.

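### The adverse event relatedness list has no category for the trial-required clopidogrel and aspirin, so antiplatelet harm cannot be separated in either arm

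*Protocol*

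**What the plan says.** Section 9, item 2 (Anticipated Adverse Events) gives the relatedness rule: events "will be identified as either device related, procedure related or “other” (such as pre-existing conditions". Further down, the same item adds a timing consideration: "Strong consideration will be given in the determination of procedure or device related for events occurring within 30 days of the procedure".

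Section 6.1 describes the drug regimen of the closure arm: "This therapy will include 75mg of clopidogrel and 100mg of aspirin daily for the first three months", followed by aspirin alone up to month six. For the other arm it says that "the control group will not receive PFO closure surgery but will still need to undergo antiplatelet therapy for six months", on the same regimen. Table 1 lists both drugs under Interventions, next to PFO closure.

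The protocol expects these drugs to cause some harm. Section 8 has a discontinuation criterion for adverse events "including allergy to antiplatelet drugs or intolerable side effects". The list of anticipated events in section 9 contains "Allergic drug reaction – idiosyncratic reaction to drugs used" and also bleeding. Exclusion criterion 6 screens out people with contraindications to antiplatelet therapy.

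On collection, section 9 is broad: "All adverse events occurring after enrollment (enrollment is defined as point of randomization) for either study group will be collected". The stated safety outcome in section 10.2 is the incidence of adverse events, and their analysis is referred to the statistical plan.

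**The concern.** The relatedness list names two of the three things the trial gives to participants, the device and the procedure. The third, the antiplatelet regimen, is the only one that both arms receive and the only one that controls receive. A harm caused by it has no label of its own and falls into *other*, where the single example offered is pre-existing conditions.

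The separability of harms is at stake. If the cause is never recorded as drug related, no later analysis can recover it reliably from the relatedness field. In the closure arm there is a second effect. An early drug-caused event can be credited to the device or the procedure, which would make closure look riskier than it is. The same event in a control participant would carry a different label.

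**Working it through.** No arithmetic is needed, because the point depends on no rate, margin, error level or sample size. The check sets the labels against what each arm receives.

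**Inputs**
- Labels: device, procedure, *other* (section 9, item 2).
- Exposure: closure plus antiplatelet drugs in one arm, antiplatelet drugs only in the other (section 6.1, Table 1).
- Events covered: all adverse events from randomization, both arms (section 9).
- Timing consideration: 30 days after the procedure (section 9, item 2).

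**Step 1. Label available for each cause**

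| Cause of the event | Closure arm | Control arm, treated as assigned |
| --- | --- | --- |
| Device | device related | not exposed |
| Closure procedure | procedure related | not exposed |
| Clopidogrel or aspirin | *other* (early events lean to device or procedure) | *other* |
| Pre-existing or unrelated condition | *other* | *other* |

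The last two rows cannot be told apart in the control arm. In the closure arm they can differ only by being misattributed to closure.

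**Step 2. Is a drug category given elsewhere?** None appears in the protocol. Section 8 mentions antiplatelet allergy and intolerance, but as a reason for discontinuation, so it covers only those who stop. The anticipated list names types of event and not their causes. A bleed in the closure arm could come from the access site or from the drugs, and the event name does not say which.

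**Step 3. Does the relatedness rule reach drug harms?** Yes. It stands under the anticipated events, and allergic drug reaction and bleeding are both on that list.

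**Step 4. Do the arms differ in how the same event is coded?** Take a bleed caused by the antiplatelet drugs within 30 days. In the closure arm the adjudicators are told to give strong weight to device or procedure. In the control arm only *other* is open. Treatment is open-label. The only body described as blinded is the Event Board, whose remit is the neurological endpoints, whereas the DSMB has the final say on adverse event categories.

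**Step 5. What is not touched?** Events are collected in both groups whatever their cause. A count of all adverse events, or of all serious adverse events, by arm does not use the relatedness label.

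**Scope.** All 110 planned participants take the drugs for 24 weeks. With 1:1 allocation, 110 / 2 = 55 are controls, for whom one of the three labels is usable. The documents give no rate of antiplatelet-caused events, so the number affected cannot be stated.

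**The case against.** The strongest case on the other side has five parts.

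- *The randomised contrast is closure, and the drugs are common background.* This stands as far as it goes. With the same regimen in both arms, a comparison of all-cause events remains sound. It does not help a reader who wants to know which harms belong to closure and which to the drugs.
- *Some drug harms can be found without a relatedness label.* This is partly true. Allergic reactions, bleeding and antiplatelet discontinuations can be tabulated by arm. For bleeding in the closure arm, however, the event type leaves the cause open.
- *The DSMB may refine adverse event definitions during the study.* That offers a route to correction, but a change partway through risks coding early and late events differently.
- *The 30-day sentence is guidance.* This stands. Strong consideration is not assignment, so the lean towards device or procedure is a risk whose size is unknown.
- *This belongs in the statistical analysis plan.* Tabulation does. The list of permitted attributions is a recording rule fixed in the protocol, and a category that was never recorded cannot be tabulated later.

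Two stronger readings are tempting and should be resisted. A reader might infer that drug harms are classed as unrelated to the trial. The text says *other*, with pre-existing conditions as an example, so the label is uninformative about the drugs and does not deny a link. The class of *Other events* in the same section, meaning reports judged not to be adverse events, is also a different thing. A reader might further infer that the between-arm safety comparison would be wrong. The protocol states no between-arm comparison of related events, and its stated safety outcome does not depend on attribution.

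**Conclusion.** The point holds as a gap in attribution. The relatedness list omits a trial-required intervention given to every participant, although the protocol itself foresees that intervention's harms. As a result, antiplatelet harm cannot be separated from pre-existing conditions in either arm, control events have one possible label, and device and procedure risk may be overstated in the first 30 days. All-cause adverse event incidence by arm is not affected, nor is any efficacy endpoint, test or sample size.

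The conclusion assumes that the list is applied as printed, that controls are treated as assigned (a control who underwent closure could receive the other labels), and that the adverse event form, which is not shown, adds no drug category. It is a modest defect, worth correcting because it is cheap to change now and hard to reconstruct afterwards.

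**What to change.** In section 9, item 2, and on the adverse event form:

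1. Add *antiplatelet-drug related (clopidogrel or aspirin)* to device related, procedure related and *other*.
2. Allow more than one attribution for an event.
3. State that the categories are applied in the same way in both arms.
4. State that the 30-day consideration does not displace the antiplatelet category.

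Events already classified should be reviewed once under the new list, so that early and late coding agree.

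The cost is one form field, a few sentences in section 9 and slightly more adjudication work for the existing DSMB, including that single review. No visit, test, participant or change to treatment is needed.

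### The only named bleeding term covers severe bleeds alone, so a bleeding rate reported under it would be too low, although lesser bleeds are still collected as adverse events

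*Protocol*

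**What the plan says.** Section 9 of the protocol (Adverse Events) gives a list of anticipated adverse events. Its one bleeding entry reads "Bleeding – loss of blood from vascular system requiring 1 unit of blood or >5g/dl drop in Hb". The list has no second entry for lesser bleeding. The nearest other term, vascular access site injury, gives only AV fistula and aneurysm as examples.

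Before the list, section 9 defines serious adverse events, adverse events and other events, and then states: "The above mentioned definitions will be applied to the following events to categorize severity". The list is introduced as open: "These potential events include, but are not limited to".

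The general definition in section 9 has no severity threshold: "Adverse events are defined as an undesirable health occurrence or untoward deviation in health away from baseline, whether or not device or procedure related". All such events after randomisation "for either study group will be collected on the adverse event form and analyzed according to the statistical plan". Section 10.2 makes the incidence of adverse events a secondary outcome.

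On exposure, section 6.1 says of the surgical group: "This therapy will include 75mg of clopidogrel and 100mg of aspirin daily for the first three months". Aspirin alone follows to month six. Controls "will still need to undergo antiplatelet therapy for six months with the same medication regimen as the surgical intervention group".

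**The concern.** Section 9 sets an order: name the event, then grade it as serious, non-serious or other. The bleeding entry departs from that order because the name already requires a transfusion or a large fall in haemoglobin. A bleed that meets either limb will usually be serious under the protocol's own definition, which includes medically significant events and laboratory abnormalities. The non-serious grade is then close to empty for this term, and lesser bleeds have no bleeding term to go to.

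This matters because every participant is exposed to antiplatelet drugs, and exclusion criterion 6 in section 5.2 treats active and visceral bleeding as contraindications to them. Attribution in section 9 is limited to device, procedure or other, with no category for the drugs. The event name is therefore the main place where bleeding would be visible. At stake are the absolute bleeding rate in each arm and the visibility of any extra bleeding around the procedure, in a trial whose summary refers to a high safety profile.

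**Working it through.** The protocol states no bleeding figure, so there is nothing to reproduce. The check is a reading of the rules, followed by an illustration on assumed rates.

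**Step 1: follow two bleeds through section 9.**

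| | Bleed needing 1 unit of blood | Bleed with a 4 g/dl fall, no transfusion |
|---|---|---|
| Meets the general adverse event definition? | Yes | Yes |
| Recorded on the adverse event form? | Yes | Yes |
| Meets the Bleeding entry? | Yes | No (no transfusion, and 4 is not more than 5) |
| Graded serious or non-serious? | Yes | Yes; serious if, for example, it leads to hospital admission |
| Counted in overall adverse event incidence? | Yes | Yes |
| Counted under Bleeding? | Yes | No |

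The two differ in the Bleeding label and in any count made by that label. They do not differ in capture.

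**Step 2: what determines the shortfall.** Let N be the number of participants, p the risk of any bleed, and s the share of bleeding participants who meet the threshold.

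- Participants with any bleed: N × p
- Participants counted under Bleeding: N × p × s
- Ratio of the reported rate to the any-bleed rate: s

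The relative understatement is therefore 1 − s. The documents give neither p nor s.

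**Step 3: illustration.** N = 110 (section 11). Both p and s are assumptions, varied over wide ranges: p from 5% to 20%, s from 5% to 50%.

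| p | s | Any bleed (110 × p) | Counted as Bleeding (110 × p × s) | Chance that none is counted, (1 − p × s)^110 |
|---|---|---|---|---|
| 5% | 5% | 5.5 | 0.28 | 0.76 |
| 5% | 50% | 5.5 | 2.75 | 0.06 |
| 10% | 10% | 11 | 1.1 | 0.33 |
| 20% | 5% | 22 | 1.1 | 0.33 |
| 20% | 50% | 22 | 11 | below 0.001 |

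The term would hold about 0.3 to 11 participants out of 5.5 to 22. The direction is fixed by the definition (s cannot exceed 1), but the size depends wholly on s.

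**Step 4: the haemoglobin limb.** Section 6.2 lists blood tests at baseline, and Table 1 shows no haemoglobin test in follow-up. This is weak evidence. Section 10.2 includes unspecified laboratory indicators among the outcomes, and Table 1 also omits video EEG and cardiac ultrasound, which are outcomes too. The transfusion limb needs no serial measurement. I put no weight on this step.

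**The case against.** The strongest reply is that this is a matter of labelling. Section 9 collects all adverse events in both arms without a threshold, treats any reported event that is neither serious nor other as an adverse event, and leaves the anticipated list open. A lesser bleed is recorded, graded and counted in a secondary outcome. The protocol nowhere says that bleeding will be tabulated only under this term, and the statistical plan to which it refers is not at hand. Other entries also carry thresholds (fever, blood pressure, valvular regurgitation). The DSMB may refine the definitions and has the final say on categorisation.

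Most of this stands, and it rules out several stronger readings that a reader might infer:

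- *Most bleeding would go unreported.* Not supported. Lesser bleeds are reported as adverse events, and whether they are most bleeds depends on an assumed share.
- *Antiplatelet harm would be understated in the comparison of arms.* Not supported. Both arms take the same regimen, so no definition of bleeding lets that comparison isolate the drugs' effect.
- *The entry contradicts the general adverse event definition.* It does not. A narrow term in an open list leaves the general definition in force.
- *The entry contradicts section 8.* That section allows discontinuation for "Adverse events occurred during the trail, including allergy to antiplatelet drugs or intolerable side effects, etc". A bleed that ends participation this way is still an adverse event, whatever its label.
- *Bleeding is the main expected harm of the regimen.* The protocol does not say so. Exclusion criterion 6 shows only that the hazard is recognised.

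The objection does not remove the mismatch between the bleeding entry and the rule that severity is graded after naming. The definition is fixed in the protocol, so any table built on that term inherits the threshold. The DSMB's power to refine definitions is a route to the correction.

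**Conclusion.** The point holds in a limited form. The protocol's only named bleeding term admits severe bleeds alone, although section 9 grades severity separately and every participant takes antiplatelet therapy for six months. Lesser bleeds are collected and graded but fall outside the Bleeding category, so a bleeding rate reported under that term would be too low.

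The size cannot be computed from the documents. On the assumed ranges above, the term would capture anywhere from 5% to half of the participants who bleed, and those limits are simply the assumed share. The consequence also depends on bleeding being summarised by this term, which the protocol neither states nor excludes. This is an inexpensive improvement to a definition. It does not show that safety data would be lost.

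**What to change.** In the anticipated-event list of section 9:

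1. Define Bleeding as any reported bleeding event after randomisation.
2. Grade each event as serious or non-serious by the definitions already in section 9.
3. Keep the present criterion (1 unit of blood, or a haemoglobin fall of more than 5 g/dl) as a named severe subset.
4. Report any bleeding and severe bleeding, each by arm.

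The DSMB's remit in section 9 already allows definitions to be refined. The change should be made before the data are analysed, so that events are not recoded after results are known.

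The cost is one reworded definition and one additional row or table. The adverse event form already collects the events, and no dose, visit or clinical rule changes. The downside is that the reported bleeding rate will be higher; the severe subset keeps the present definition available beside it.
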